## Abstract

**Abstract:**

Interventional radiology (IR) has evolved rapidly, but the clinical integration of interventional radiologists has not kept pace with technical advancements. This trial will address a gap in the literature by providing a robust investigation into specific measures for enhancing the clinical role of interventional radiologists, with potential implications for improving patient experiences and outcomes. The single-center randomized controlled trial will include 428 patients undergoing IR procedures. The control group will receive information about the procedure from the ordering physician, while the experimental group will have an additional consultation with an interventional radiologist and be shown procedure-specific explanatory videos. The primary outcomes are patients’ knowledge, satisfaction with the information and communication, and anxiety. Data collection will involve specific questionnaires and scales. This trial is designed to investigate the importance of proactive clinical roles in patient care within IR. The study explores the potential of consultations and audiovisual tools, highlighting their role in educating patients about procedures. The results may help foster a more widespread acceptance of clinical responsibilities in IR and underscore the pivotal role of audiovisual aids in patient education and satisfaction.

**Trial registration:**

NCT05461482 at clinicaltrials.gov.

**Relevance statement:**

This randomized controlled trial will assess the impact of clinical consultations and explanatory audiovisual tools on patient understanding, satisfaction, and anxiety in interventional radiology. The findings could help establish a more proactive clinical role for interventional radiologists and improve the overall quality of patient-centered care.

**Key Points:**

We describe the protocol of an interventional radiology randomized clinical trial.The control group will receive procedure information from the referring physician and the experimental group receives additional consultation with interventionalists and views a video.Knowledge, satisfaction with information, and patient anxiety will be evaluated.This study will provide insights about the benefits of consultations and videos in interventional radiology.

**Graphical Abstract:**

[figure not shown]

## Background

Interventional radiology (IR) has developed rapidly since its inception in the 1960s and has now become an essential part of modern medicine [1, 2]. However, the swift development of IR techniques has not been accompanied by the emergence of a clinical role for interventional radiologists [3–5]. The movement of IR toward a more clinical role focused on patient care (before, during, and after interventions) has been slow and heterogeneous due to various interrelated factors [3]: the disparate recognition of IR as an area of knowledge differentiated from other specialties and subspecialties and the consequent lack of standardization of official IR training [6]; the historical origins of IR in traditional radiology [7, 8]; the lack of training of interventional radiologists in clinical skills [3]; and the lack of infrastructure and professional resources [8].

IR scientific societies and experts agree that the cornerstone for the consolidation of IR is its transition to an active clinical role. However, the existing bibliography about the impact of specific measures for developing this clinical role in IR is limited [9–11].

This randomized controlled trial (RCT) intends to evaluate whether the implementation of IR clinical consultations and the use of videos to explain the procedures have an impact on patients’ understanding of the procedures, their satisfaction with the information provided, and the anxiety they experience related to the procedures. To the best of our knowledge, this is the first RCT investigating this issue.

## Objectives and study design

The CLINTERVENTIONAL study is a single-center, two-arm RCT, registered at clinicaltrials.gov (NCT05461482). In the control arm, patients will be informed about the IR procedure by the ordering physician, which is the usual process in the hospital. In the experimental arm, patients will have an additional consultation with an interventional radiologist and will be shown an explanatory video about the procedure. This trial is independent of industry funding. It has been initiated and conducted with resources from the Maimónides Biomedical Research Institute of Córdoba and Reina Sofía University Hospital (Córdoba, Spain). The study protocol, informed consent form template, and other requested documents regarding both the scientific content and compliance with applicable regulations regarding research and human subjects have been reviewed and approved by the Research Ethics Committee of Córdoba. The trial will be conducted in accordance with the Declaration of Helsinki.

Participants will receive a clinical trial information sheet and must provide written informed consent (Appendix 1: Clinical trial information sheet and sample informed consent form). The allocation of patients will be done using random number tables with a 1:1 allocation ratio. The participants, data analysts, and outcome evaluators will be blinded to the arm assignment.

The main objective is to assess and compare both groups at baseline and after the IR procedure in terms of patients’ level of knowledge and understanding of the IR procedures, patients’ satisfaction with the information provided and the method of communication, and patients’ anxiety

There are four secondary objectives. The first is to analyze changes within each group in patients’ level of knowledge and understanding of the IR procedures, patients’ satisfaction with the information provided and the method of communication, and patients’ anxiety at the beginning of the RCT and at the end. The second is to analyze and compare the duration of the intervention, the patients’ perceived pain intensity during the procedure, the level of tolerance for the intervention, and the patients’ satisfaction level with the intervention performed. The third is to evaluate the association of different variables (demographics, personal history, assigned arm, type of IR procedure, anxiety related to the IR procedure, knowledge and understanding of the IR procedure, type of anesthesia, and degree of sedation) with the intensity of pain during the intervention, tolerance of the procedure, and satisfaction with the intervention. The fourth is to evaluate explanatory videos as an educational tool.

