**Other variables**					
Demographic variables	Sex, age, marital status, and educational level	1st			
Personal history	Previous IR procedures, other types of interventions, history of anxiety and depression, and previous knowledge of IR	1st			
Procedure-specific variables	Preparation method, anesthesia type, sedation level (Ramsay Sedation Scale), and procedure duration				4th
Pain intensity during the procedure	10-point VAS^c^				4th
Intervention tolerance level	10-point VAS^b^				4th
Satisfaction level with the intervention	10-point VAS^b^				4th
Usefulness of explanatory videos	10-point VAS^b^ and dichotomous questions^d^		2nd		

*IR* Interventional radiology, *STAI* State-Trait Anxiety Inventory, *VAS* Visual analog scale

^a^ Data collection times: 1st (screening visit), 2nd (after the consultation with the radiologist, only for the experimental group), 3rd (on the day of the procedure, before it is performed), and 4th (on the day of the procedure, after it is performed)

^b^ VAS, where 1 represents the minimum value and 10 the maximum value

^c^ VAS for pain, where 0 indicates no pain, 1–3 mild pain, 4–6 moderate pain, 7–8 severe pain, and 9–10 excruciating pain

^d^ The questions are: Did you find the video useful for better understanding the intervention? Did you like the video as an explanatory tool? Do you feel less anxiety after watching the video? Do you understand the intervention better after watching the video?

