### Data collection and statistics

Trained research coordinators will supervise the questionnaires without participating in clinical care. Data collection will be conducted with digital and paper questionnaires. The results will then be uploaded into a dedicated database and organized for data extraction. Data managers will be responsible for data entry. To ensure robust data quality control, a subset of patients will be randomly selected for double data entry. This meticulous approach serves as the primary mechanism for validating data accuracy, with thorough verification procedures used to address any inconsistencies identified. The information collected will remain anonymous; a three-digit code will be used to identify patients. The data will be retained for at least 25 years after completion of the study, in compliance with regulations. Digital files will be stored on institutional computers and protected with passwords, while paper copies of the questionnaires will be securely stored at research facilities.

Descriptive statistics will be used to calculate absolute and relative frequencies for qualitative variables and mean and standard deviation for quantitative variables. Confidence intervals with 95% confidence intervals will be calculated.

For comparisons of quantitative variables, parametric tests will be used if the data will follow a normal distribution: Student’s *t*-test for independent data and a one-way analysis of variance when comparing independent groups and Student’s *t*-test for paired samples and repeated measures analysis of variance in the case of paired samples. In addition, a mixed analysis of variance will be performed to compare intragroup and intergroup variability at the same time. If the data do not follow the normal distribution, nonparametric tests will be used. For comparisons of qualitative variables, the *χ*^2^ test will be used for comparisons of independent data and the McNemar’s test and Cochran’s *Q* test for paired samples.

Finally, a multiple logistic regression analysis (manual stepwise method) will be performed in order to obtain an associative model among the variables of pain intensity during the procedure, level of tolerance of the procedure, and satisfaction with the intervention and the rest of the covariates potentially considered as such.

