All comparisons will be two-tailed and considered significant when *p* < 0.05. The data will be stored, processed, and analyzed using SPSS® Version 28.0 (IBM, Armonk, NY, USA).

The sample size has been calculated using the GRANMO sample size calculator. Based on a study by Lattuca et al [13], a difference equal to or greater than 1 on the knowledge and understanding score (standard deviation, 3.5) was assumed. Hence, the estimated effect size (Cohen’s *d*) was 0.285. Additionally, a bilateral design, an alpha risk of 0.05, a beta risk of 0.2, an allocation ratio of 1, and a loss-to-follow-up rate of 10% were established. Therefore, 214 subjects in the control group and 214 in the experimental group would be required. No strategies will be used to foster quicker enrollment.

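### The first secondary objective attaches uncontrolled before-after tests to each arm; conclusions about change should rest on the baseline-adjusted difference between arms

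*Protocol article*

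**What the plan says.** The main objective, under Objectives and study design, is a comparison between arms: "The main objective is to assess and compare both groups at baseline and after the IR procedure", covering knowledge, satisfaction and anxiety. The first secondary objective then takes the same measures one arm at a time: "The first is to analyze changes within each group", from the start of the trial to its end.

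For normally distributed paired data, Data collection and statistics names the paired t-test and "repeated measures analysis of variance in the case of paired samples", with nonparametric tests otherwise. It also plans independent-samples tests, and "a mixed analysis of variance will be performed to compare intragroup and intergroup variability at the same time". The threshold is general: "All comparisons will be two-tailed and considered significant when" p is below 0.05.

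Table 2 lists the main measures at the 1st, 2nd and 3rd times. Its footnote a defines the 2nd time as "2nd (after the consultation with the radiologist, only for the experimental group". The experimental arm therefore completes these measures three times and the control arm twice.

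The 3rd time is on the procedure day, before the procedure, and Table 2 shows no later collection of the main measures. I therefore take the end of the trial to be the 3rd time. The main objective speaks of a comparison after the procedure, and that wording needs reconciling with Table 2.

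**The concern.** A change within one arm is a before-after comparison without a randomized control. According to Study cohort and outcome measures, controls are informed by the ordering physician before enrolment and are given nothing further. Their change from the 1st to the 3rd time therefore contains no trial intervention. It reflects whatever else moves the scores: sitting the same questionnaire again (for knowledge, one 12-question form per procedure) and being closer to the procedure (most plausibly for anxiety). The same influences enter the experimental arm's change, where a paired test cannot separate them from the consultation and video.

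The two within-arm results are also not like for like, because one arm has had an extra sitting. And a p-value in one arm set beside a p-value in the other is not a test of whether the arms differ. Improvement in the experimental arm with no significant change in controls is a pattern that can appear when the arms do not differ at all.

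**Working it through.** **The plan's own sample size.** Inputs from Data collection and statistics: difference 1 point, SD 3.5, two-sided alpha 0.05, power 0.80, 10% loss.

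n per arm = 2 × [3.5 × (1.960 + 0.842) / 1]² = 192.3, and 192.3 / 0.9 = 213.7, so 214. The stated figure is reproduced. The evaluable number is about 193 per arm.

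**Chance that exactly one arm is significant.** Let p be the probability that a two-sided paired test at 0.05 is significant in one arm. The arms are independent and, by assumption, share the same true change. Then

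P(exactly one arm significant) = 2p(1 − p), and P(experimental arm only) = p(1 − p).

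- No change, p = 0.05: 2 × 0.05 × 0.95 = 9.5%; experimental arm only 4.75%.
- p = 0.50: 2 × 0.5 × 0.5 = 50%, the maximum; experimental arm only 25%.
- p = 0.80: 2 × 0.8 × 0.2 = 32%; experimental arm only 16%.

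With 193 per arm, 50% power needs a shared change of 1.960 / √193 = 0.14 SD of the change score, and 80% power needs (1.960 + 0.842) / √193 = 0.20 SD.

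**In points on the knowledge score.** SD of change = 3.5 × √[2(1 − r)], where r is the correlation between the two visits. The protocol gives neither r nor a shared change, so both are assumed over a range. Each cell shows the chance that exactly one arm is significant, with experimental arm only in brackets.

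| Shared change (points) | r = 0.3 (SD 4.14) | r = 0.5 (SD 3.50) | r = 0.7 (SD 2.71) |
|---|---|---|---|
| 0 | 9.5% (4.8%) | 9.5% (4.8%) | 9.5% (4.8%) |
| 0.25 | 23.2% (11.6%) | 28.0% (14.0%) | 37.4% (18.7%) |
| 0.50 | 47.5% (23.8%) | 50.0% (25.0%) | 39.7% (19.9%) |
| 0.75 | 41.1% (20.6%) | 26.1% (13.1%) | 5.8% (2.9%) |
| 1.00 | 15.0% (7.5%) | 4.4% (2.2%) | 0.2% (0.1%) |

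The figure is not monotone. It peaks where each test has about 50% power and falls below 9.5% once the shared change is large. In that region the other problem takes over: at r = 0.5, a shared change of 0.75 points is significant in both arms in about 71% of simulated trials, whatever its cause.

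**The direct comparison.** In simulations of 10,000 trials per scenario (shared change 0 to 0.75, the same three correlations), a single two-sample test of the change between arms was significant in 4.6% to 5.5% of trials.

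**Precision of the adjusted comparison.** Relative to the unadjusted 3rd-time comparison, adjusting for the 1st-visit score multiplies the variance by about 1 − r²: 0.91, 0.75 and 0.51 for r = 0.3, 0.5 and 0.7. A comparison of change scores multiplies it by 2(1 − r): 1.4, 1.0 and 0.6.

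**The case against.** The strongest reply is that the valid analysis is already there. The main objective is between arms, the trial is sized on a between-arm difference, and the mixed ANOVA can test whether change differs by arm. Within-arm change is kept apart as a secondary objective, and 95% confidence intervals are already planned. All of this stands.

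A reader might infer that the trial will claim benefit from significance in one arm only. The document does not say so; nothing in it sets one arm's p-value against the other's or bases efficacy on within-arm tests. Nor is 50% the expected rate. It is the worst case, and the favourable pattern is half of any discordance.

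A reader might also add regression to the mean as a cause of shared change. Table 1 does not select patients on knowledge, satisfaction or anxiety scores, so the document gives no support for that. Learning from retesting mainly concerns the knowledge form; the satisfaction scales and the STAI have no correct answers to learn.

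Finally, which result carries a conclusion may be settled in a fuller protocol or an analysis plan that is not shown. What remains is what this document does fix: a within-arm objective, paired tests to serve it, and a significance threshold that covers every comparison.

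**Conclusion.** The point holds as a minor one. The first secondary objective, with its paired tests at p < 0.05, yields before-after p-values that cannot isolate the intervention. With no true difference between arms, exactly one arm is significant in 9.5% of trials per outcome if nothing changes, and in up to 50% for a modest shared change; the experimental arm alone accounts for half of these.

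The rates assume independent arms, an equal true change and about 193 evaluable patients per arm. Where a trial falls in the range depends on a shared change and a between-visit correlation that the protocol does not give. The rates are per outcome; I have not combined them over the five main measures, because the correlation between measures is unknown.

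The main between-arm comparison is not undermined by this objective. The experimental arm's extra sitting is a separate matter: a retest effect could differ by arm and so enter the between-arm comparison as well.

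**What to change.** - Report within-arm changes as means with 95% confidence intervals, without p-values.
- State that inference on change rests on the between-arm difference at the 3rd time, adjusted for the 1st-visit score. That score is already collected, and the adjusted comparison is usually more precise than the unadjusted t-test.
- Describe the experimental-only 2nd assessment separately and leave it out of the between-arm model, since controls have no such measurement. If the mixed ANOVA is kept, confine it to the 1st and 3rd times, where its arm-by-time term tests the difference in change.
- Acknowledge the experimental arm's extra sitting as a limitation. None of these changes removes it.

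The cost is a few sentences of wording, with no new data and no change to the sample size. The downside is fewer within-arm p-values to report.

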### Study cohort and outcome measures

Patients who are planned to undergo an IR procedure at the Reina Sofía University Hospital will be candidates for participation in the trial. Full inclusion and exclusion criteria are provided in Table 1.

**Table 1 Tab1:** Eligibility criteria

Inclusion criteria	Exclusion criteria
Patients undergoing one of the following vascular or non-vascular procedures: • Endovascular recanalization; • Placement of tunneled central venous catheters; • Fistulograms and endovascular treatment of hemodialysis fistulas; • Endovascular embolization; • Percutaneous biopsies; • Percutaneous drainage of collections; • Percutaneous transhepatic biliary drainage; • Percutaneous nephrostomies.	• Patients under 18 years of age. • Patients requiring the involvement of a third party for informed consent. • Pregnant patients. • Patients undergoing urgent interventional procedures. • Patients with allergies or intolerance to mepivacaine, tramadol, midazolam, or fentanyl. • Patients who do not understand and speak Spanish proficiently. • Patients with deafness or blindness.

The study design flowchart is shown in Fig. 1, which provides a schematic overview of key time points.

**Fig. 1 Fig1:**
[figure not shown]
Flowchart illustrating the study design, showing a schematic summary of critical time points throughout the trial

After their cases have been presented to a multidisciplinary board or discussed between physicians, patients will be informed about the IR procedure (objectives, benefits, risks, alternatives, etc.) by the ordering physician, according to the usual procedure in our hospital. Next, patients will be seen by the trial coordinators, who will inform them about the clinical trial, invite them to participate, and explain the informed consent procedure. After that, subjects who agree to participate will be randomly assigned to the control group (in which no more information will be provided) or to the experimental group. Randomization will be conducted by an independent coordinator using random number tables specific to each procedure included in the study.

Subjects in the experimental group, in addition to receiving the same information as the control group, will have a consultation with an interventional radiologist, who will explain the IR procedure in detail. Subjects in the experimental arm will also be given a leaflet that explains the preparation for the procedure, its objectives, the expected benefits and associated risks, and what they can expect once it is performed. In this leaflet, a QR code will take patients to an animated video that explains this information in a clear, easy-to-understand format. Eight videos have been made, one for each type of procedure included in the trial (endovascular recanalization, placement of tunneled central venous catheters, fistulograms, and endovascular repair of hemodialysis fistulas, endovascular embolization, percutaneous biopsies, percutaneous drainage of collections, percutaneous transhepatic biliary drainage, and percutaneous nephrostomies), which last approximately four minutes each. See Appendix 2: leaflets with QR codes enabling access to the corresponding videos—one for each IR procedure.

The variables that will be analyzed, the methods used to evaluate them, and the different points in time in which they will be analyzed are shown in Table 2. Knowledge and understanding of the interventions will be assessed by means of 12-question multiple-choice questionnaires. The scoring system for these questionnaires awards 1 point for each correct answer. The questionnaires consist of five blocks of questions: those regarding the procedure itself, preparation, benefits, risks, and care following the procedure. These questionnaires have been developed following a systematic approach to ensure their validity and reliability. A comprehensive literature review was first conducted to identify relevant items used in similar studies [12–16]. A preliminary version was then prepared, which was discussed and revised by all authors, adjusting it to fit the study’s purpose. Finally, a pilot test was performed with a sample of 16 patients who met the selection criteria. During this phase, patients provided feedback through structured interviews, which allowed adjustments to be made to improve the clarity and applicability of the questionnaires. The final validated version of the questionnaires is presented in Appendix 3.

**Table 2 Tab2:** Variables, measurement method, and data collection times

Variables	Measurement method	Data collection time^a^			

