**Main variables**					
Knowledge and understanding of the procedure	12-point specific multiple-response questionnaire for each procedure (see Appendix 3)	1st	2nd	3rd	
Satisfaction with the method of communicating information	10-point VAS^b^	1st	2nd	3rd	
Satisfaction with information transmitted	10-point Visual Analog Scale^b^	1st	2nd	3rd	
Anxiety related to the procedure	STAI questionnaire and 10-point VAS^b^	1st	2nd	3rd	

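### The simple between-arm tests leave out procedure, although procedure defines both the randomization lists and the knowledge questionnaire: precision is lost, validity is not

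*Protocol article*

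**What the plan says.** **Allocation** (Study cohort and outcome measures): "Randomization will be conducted by an independent coordinator using random number tables specific to each procedure included in the study". Eight procedures are eligible. The article does not say whether the lists are blocked.

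**Knowledge score** (Table 2, main variables): "12-point specific multiple-response questionnaire for each procedure (see Appendix 3". Information satisfaction and anxiety use instruments common to all procedures.

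**Between-arm tests** (Data collection and statistics): "Student’s *t*-test for independent data and a one-way analysis of variance when comparing independent groups", with nonparametric tests if the data are not normal. The same section adds that "a mixed analysis of variance will be performed to compare intragroup and intergroup variability at the same time". None of these names procedure as a factor.

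**Where procedure does enter:** the third secondary objective (Objectives and study design) lists "assigned arm, type of IR procedure, anxiety related to the IR procedure" among the variables to be related to pain, tolerance and satisfaction with the intervention. The matching analysis reads "a multiple logistic regression analysis (manual stepwise method) will be performed in order to obtain an associative model among the variables of pain intensity". Duration is compared between arms under the second secondary objective but is not an outcome of that regression.

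**Sample size** (Data collection and statistics): "a difference equal to or greater than 1 on the knowledge and understanding score (standard deviation, 3.5) was assumed". Knowledge is treated as one score pooled over procedures.

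**The concern.** Procedure is built into the design twice: it determines which list allocates the patient and which knowledge test the patient sits. An analysis that pools all patients without it counts every difference between procedures as noise.

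For knowledge, that noise includes any difference in difficulty between the eight questionnaires. The article describes a common format and a pilot in 16 patients, or two per questionnaire if spread evenly (16/8). The pilot collected feedback on clarity and applicability, so it does not establish equal difficulty.

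Duration is the most exposed outcome. It is recorded once, has no baseline, and would pool catheter placements with embolizations in a single unadjusted test. Pain, tolerance and satisfaction with the intervention are also recorded once. At stake is the width of the confidence intervals and some power.

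**Working it through.** **Inputs from the article:** difference 1, SD 3.5, two-sided alpha 0.05, power 0.80, 1:1 allocation, 10% loss, eight procedures. **Assumed:** r, the share of the score variance that lies between procedures, taken as 0 to 30%, with 3.5 as the SD pooled over procedures.

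**1. The plan's own figure.** n per arm = 2 × 3.5² × (1.960 + 0.842)² / 1² = 192.3, and 192.3/0.9 = 213.7, so 214 per arm. The stated size reproduces and is not in question. The rest uses 193 evaluable per arm.

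**2. Standard errors.** Unadjusted: 3.5 × √(2/193) = 0.356. Adjusted for procedure: 0.356 × √(1 − r), which is 0.338, 0.319 and 0.298 for r = 10%, 20% and 30%. The confidence interval narrows by 1 − √(1 − r), about 5%, 11% and 16%.

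**3. Power and type I error.**
- Adjusted power: Φ(1/SE_adj − 1.96).
- Unadjusted power, unblocked lists: Φ(1/0.356 − 1.96) = 80.1% at every r, because chance imbalance between procedures is real variation that the unadjusted SE correctly includes.
- Unadjusted power, arms balanced within procedure: Φ((1 − 1.96 × 0.356)/SE_adj). The true variability is the smaller one, but the test still uses 0.356.
- Unadjusted type I error, balanced lists: 2 × (1 − Φ(1.96/√(1 − r))).

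| r | Adjusted power | Unadjusted power, unblocked | Unadjusted power, balanced | Unadjusted type I error, balanced |
|---|---|---|---|---|
| 0 | 80.1% | 80.1% | 80.1% | 0.050 |
| 10% | 84.1% | 80.1% | 81.4% | 0.039 |
| 20% | 88.1% | 80.1% | 82.8% | 0.028 |
| 30% | 91.8% | 80.1% | 84.4% | 0.019 |

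In patients, the adjusted model reaches 80% power with 174, 154 or 135 evaluable per arm at r = 10%, 20% or 30%, against 193 for the unadjusted test with unblocked lists.

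**4. Simulation** (386 patients, eight procedures, 4000 runs per setting). With balanced lists, the t-test's type I error was 0.035 at r = 10% and 0.025 at r = 20%. With unblocked lists it was 0.047 and 0.048, so it is not inflated. Adjusted power was 84.5% and 88.3% with balanced lists, and 83.0% and 87.8% with unblocked lists.

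**5. Mixed ANOVA.** Each patient answers the same procedure's questionnaire at each time, so a stable procedure effect cancels in the change from baseline. The change has variance 2 × (1 − ρ) times the within-procedure variance, where ρ is the within-patient correlation. At an assumed ρ = 0.5 this equals the within-procedure variance. The simulated group-by-time test accordingly had power of 84.8% (r = 10%) and 88.3% (r = 20%) with balanced lists, about the same as the procedure-adjusted model. A lower ρ would give less.

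**The case against.** The strongest reply is that the plan already contains a remedy for the main variables. The mixed ANOVA's group-by-time term removes stable procedure differences, and the main objective concerns both baseline and later assessments. This stands. A reader might infer that every planned main-outcome analysis loses power, and that is not so. The article lists the mixed ANOVA as an addition to the simple tests, however, and it offers nothing for outcomes measured once.

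A reader might also infer that uneven arms across procedures would bias the comparison or produce false positives. The documents do not support this. If the lists are unblocked, chance imbalance is possible, but the unadjusted standard error covers it. If the lists are balanced, the imbalance largely disappears and the test is conservative. Over-wide intervals and uneven arms need opposite conditions and cannot be charged together.

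Nor is it shown that the eight questionnaires differ in difficulty. Appendix 3 is not reproduced, and all share twelve questions in five blocks. The argument about different tests does not reach information satisfaction or anxiety at all.

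For pain, tolerance and satisfaction with the intervention, the third secondary objective already lists arm and procedure type together. That is only partial cover, because the model is logistic and stepwise, so procedure may not be retained. Finally, an analysis plan that is not shown may add covariates. But the article does not leave the tests open: it names them, and they omit procedure.

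**Conclusion.** The point holds as a matter of efficiency. The t-test, one-way ANOVA and nonparametric comparisons between arms omit the variable that defines the randomization lists, and with it any variance between procedures that could be removed. They remain valid. Duration has no adjusted analysis at all. Pain, tolerance and satisfaction with the intervention have only a stepwise model.

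The direction is certain, but the size is not. The gain in power is about 4, 8 or 12 points against unblocked lists, or about 3, 5 or 7 points against balanced lists, for an assumed variance share of 10%, 20% or 30%. It is zero if procedures do not differ. These figures are for knowledge and take 3.5 as the pooled SD. No figure can be given for duration, because the documents contain no variance for it.

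**What to change.** In Data collection and statistics, replace the unadjusted between-arm tests of quantitative outcomes with a linear model containing arm and procedure (eight levels, fixed effect), plus the baseline value for the main variables. Use the same arm-plus-procedure model for duration, pain, tolerance and satisfaction with the intervention, with procedure kept in regardless of its p-value. Report the procedure-adjusted difference with its 95% confidence interval.

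Show the knowledge effect by procedure descriptively only. A non-significant arm-by-procedure interaction should not be read as evidence that the questionnaires are equivalent. It addresses whether the effect varies, not whether the tests are equally hard. With equal recruitment there would be about 24 evaluable patients per arm in each procedure (193/8), so each procedure's difference would have a standard error of about 3.5 × √(2/24) = 1.0 point, as large as the planned effect.

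The cost is seven degrees of freedom for procedure, out of 384 with 386 evaluable patients, and a change of wording. Procedure is known for every patient at randomization, so no new data are needed.
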